### Participant timeline {13}

The participant timeline is depicted in Fig. 1. Additionally, Fig. 2 illustrates the standard protocol items diagram according to the guidelines proposed by Standard Protocol Items: Recommendations for Interventional Trials (SPIRIT).

**Fig. 1 Fig1:**
[figure not shown]
Participant timeline. Sequence of splints (3D printed or milled) is randomized at an allocation ratio of 1:1

**Fig. 2 Fig2:**
[figure not shown]
Standard protocol items diagram according to the SPIRIT guidelines

### Sample size {14}

The sample size was calculated based on results reported for the OHIP-G14. According to the results of Alajbeg et al. [29], an OHIP-G14 score of 25.29 (SD 12.38) can be assumed for TMD patients. If the non-inferiority margin is set at 5 and a standard deviation of the differences of 10 is assumed, 38 participants are required for the trial with a two-sided paired t-test and a power of 90% on a 5% significance level. As both cohorts can be analyzed together for the primary outcome parameter OHIP-G14, the target number of cases is set at 20 participants per cohort, resulting in 40 participants in total.

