## Statistical methods

### Statistical methods for primary and secondary outcomes {20a}

Absolute and relative frequencies are calculated for binary or categorical variables. For continuous data, the median, mean and standard deviation are specified. In addition, 95% confidence intervals are calculated. The calculations are performed per group (milled and 3D printed) and per cohort (bruxism and TMD). Cross-over effects are examined in all analyses. For the primary outcome parameter OHIP-G14, the group differences are estimated and tested using a linear regression model with corresponding two-sided 95% confidence intervals. The model will include the difference in OHIP-G14 values (milled vs. 3D printed) as a dependent variable and the sequence of the splints and the cohort (bruxism and TMD) as independent variables.

The one-sided test for non-inferiority of 3D printed versus milled splints at the 2.5% significance level is based on the two-sided 95% confidence interval of the linear regression model. The null hypothesis is rejected if the lower limit of the confidence interval for the difference (conventionally milled vs. 3D printed) is above − 5. The same applies to secondary outcomes, namely volume loss of the splint/opposing dentition, pain reduction, jaw mobility, and splint fracture rates.

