### Methods in analysis to handle protocol non-adherence and any statistical methods to handle missing data {20c}

Reasons for trial discontinuation will be noted for each randomization group and the reasons will be analyzed for dependence from the randomization group and fabrication mode of the splint. Imputation of missing data is not planned; if unexpectedly a larger number of participants drops out during the trial, further participants will be enrolled to obtain the intended number of participants required for a statistical power of 90%.

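### The 38 participants stated for 90% power do not follow from the stated inputs: 38 gives 85%, the planned 40 gives 87%, and 90% needs 44.

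*Protocol article*

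**What the plan says.** Three places in the protocol article bear on this.

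- **Sample size {14}** gives the inputs: "If the non-inferiority margin is set at 5 and a standard deviation of the differences of 10 is assumed". It concludes that "38 participants are required for the trial with a two-sided paired t-test and a power of 90% on a 5% significance level". Both cohorts are pooled for the OHIP-G14, and "the target number of cases is set at 20 participants per cohort, resulting in 40 participants in total".
- **Statistical methods for primary and secondary outcomes {20a}** sets the decision rule. "The one-sided test for non-inferiority of 3D printed versus milled splints at the 2.5% significance level is based on the two-sided 95% confidence interval" of a linear regression of the paired OHIP-G14 difference on sequence and cohort, and the limit for the difference is compared with −5.
- **Section {20c} on non-adherence and missing data** plans no imputation. If an unexpectedly large number of participants drop out, more are enrolled "to obtain the intended number of participants required for a statistical power of 90" per cent.

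**The concern.** The sample size sentence gives a margin, a standard deviation, a test, a significance level and a power, so the result can be checked directly. It fails the check: the number is too small for the stated power. This is not a detail left to a fuller document, because the article gives both the inputs and a result that does not follow from them.

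Three things depend on it. This paragraph is the only justification of the trial's size, and it concerns the primary outcome. In a non-inferiority trial, low power means a higher chance that an equivalent 3D printed splint fails to be declared non-inferior. Finally, section {20c} bases enrolment on the 90% claim. That section prints no number, but whether it means 38 or 40, replacement would stop before its own criterion is met.

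**Working it through.** **Inputs**

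- Margin: 5 points (Sample size {14}; the same value as the −5 limit in {20a}).
- Standard deviation of the within-participant differences: 10 (Sample size {14}).
- Test: paired t-test at two-sided 5% (Sample size {14}). The one-sided 2.5% test in {20a} has the same critical value, so the two sections agree on alpha.
- Target power: 90% (Sample size {14} and {20c}).
- True difference: not stated. I assume 0, the usual convention.

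**Attempt to reproduce 38 by the normal approximation**

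n = (SD × (z for alpha + z for power) / margin)² = (10 × (1.960 + 1.2816) / 5)² = 4 × 10.507 = 42.03, so 43.

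The approximation is slightly optimistic for a t-test, and it already exceeds 38.

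**Exact calculation**

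Power = P(T > t critical), where T is noncentral t with n − 1 degrees of freedom and noncentrality (5/10) × √n. At n = 38 the noncentrality is 0.5 × 6.164 = 3.082 and the critical value is 2.026. At n = 40 they are 3.162 and 2.023.

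| Complete pairs | Power, paired t (n − 1 df) | Power, planned regression (n − 3 df) |
|---|---|---|
| 38 | 85.1% | 85.0% |
| 40 | 86.9% | 86.8% |
| 42 | 88.6% | 88.5% |
| 43 | 89.3% | 89.2% |
| 44 | 90.0% | 89.9% |

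So 90% needs 44 pairs with the named paired t-test. With the n − 3 residual degrees of freedom it needs 45 (90.6%). At n = 37 the paired t-test power is 84.1%, so 38 is exactly the smallest number for 85%.

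**Type II error**

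- At 38: 100 − 85.1 = 14.9%, about 1.5 times the stated 10%.
- At the planned 40: 100 − 86.9 = 13.1%, about 1.3 times.

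**Other routes to 38**

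- One-sided 5%: 90% needs 36 (90.3%), and 38 gives 91.6%. This does not produce 38, and it contradicts the alpha in both {14} and {20a}.
- One-sided 5% with 5% dropout inflation (36/0.95 = 37.9) or a rank-test allowance (36 × π/3 = 37.7): both round up to 38, but each needs the wrong alpha plus a step that the article does not mention.
- A smaller standard deviation: at two-sided 5% and 90% power, 38 pairs suffice only if it is about 9.26 instead of 10.
- A true difference in favour of 3D printing: 38 pairs suffice at about 0.40 points and 40 pairs at about 0.26 points, but the article assumes no such advantage.

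**The case against.** The arithmetic is hard to dispute, so the best case on the other side concerns weight and certainty.

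- **The trial plans 40, not 38.** The shortfall that matters is 86.9% against 90%, about 3 points. The decision rule, type I error and estimate are untouched. The standard deviation of 10 is itself an assumption, and about 9.5 would give 90% at 40 pairs. All of this stands, and it limits the practical size of the problem. It does not make the statement correct.
- **The true difference of 0 is the reader's assumption.** This also stands and should be stated openly. It does not rescue 38: nothing in the article suggests an advantage for 3D printing, and a difference against it would lower power further.
- **The article does not show which element is wrong.** The number, the power, the alpha or the standard deviation could be misreported, and the full German protocol is not shown. This bears on the remedy: the sponsor should trace the source before choosing a correction.
- **Section {20c} is a consequence, not a second error.** Agreed. It prints no number, and conditional replacement is its alternative to a dropout allowance. But neither 38 nor 40 meets the power it names, so it has to be corrected too.

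**Conclusion.** The stated sample size is wrong as written. On the article's own margin, standard deviation and alpha, with a true difference of 0, 38 complete pairs give 85% power, 40 give 87%, and 90% needs 44 (45 on the planned regression's degrees of freedom). The planned enrolment is 4 to 5 pairs short of the claim before any participant is lost. That matters because a participant without both periods contributes no paired difference and nothing is imputed.

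The power deficit at 40 is about 3 points. It does not undermine the design or the error control. It does mean that the headline power is overstated and that the replacement rule refers to a level which the planned number does not reach.

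**What to change.** First check the source calculation to see whether the number, power, alpha or standard deviation was misreported. If the margin, standard deviation and alpha stand as printed, choose one of two corrections.

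1. **Keep 40 and restate the power.** Suggested text for Sample size {14}: *Assuming no true difference, a margin of 5, a standard deviation of the differences of 10 and a one-sided 2.5% level (two-sided 95% confidence interval), 38 complete pairs give 85% power and 40 give 87%; 90% would need 44 (45 with the degrees of freedom of the planned regression).* This costs wording only, and the stated power becomes slightly less favourable.
2. **Keep 90% and raise the target** to at least 44 complete pairs, or 45 for the planned regression. This adds at least four or five participants.

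In either case, section {20c} should name the number of complete pairs that replacement enrolment aims for and the power that number gives, in place of the present reference to 90%.

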### Recruitment {15}

Dentists of the Department of Prosthetic Dentistry, Medical Centre, University of Freiburg, Germany screen patients for trial eligibility. No further strategies for achieving adequate participant enrolment are conducted to reach the target sample size since both—bruxism and TMD—are frequent in the patient population of the above-mentioned clinic.

## Assignment of interventions: allocation

### Sequence generation {16a}

The order of the splints, which can be either a milled splint first and then a 3D printed splint or vice versa, is assigned by simple randomization in a 1:1 ratio according to a computer-generated randomization scheme. This randomization scheme is created by the GraphPad Web calculator to randomly assign subjects to treatment groups.

### Concealment mechanism {16b}

Treatment order is concealed for trial participants but not for study personnel involved in treating participants since 3D printed and milled splints can be distinguished by trained clinicians.

### Implementation {16c}

The allocation scheme was generated at the start of the trial by the principal investigator (PI) who also enrolls participants. Since all participants receive the same intervention, the explanation of who will assign participants to interventions is n/a.

## Assignment of interventions: blinding

### Who will be blinded {17a}

Participants are blinded since they are not told how the splint was fabricated. Further, the statistician analyses the data generated during the trial blinded. Treating dentists cannot be blinded since trained personnel can differentiate between a 3D printed and milled splint.

### Procedure for unblinding if needed {17b}

If deemed necessary, unblinding may be performed by the study personnel who can visually differentiate between the milled and 3D printed splints. Unblinding of the participant will only be performed if it is essential for further management of the participant, for example in the case of severe allergic reactions requiring further assessment of the allergy-initiating factors.

## Data collection and management

### Plans for assessment and collection of outcomes {18a}

Data of the TMD cohort is collected and assessed by one trained and calibrated examiner according to the DC/TMD protocol. This examiner also trained the examiner collecting and assessing data of the bruxism cohort. Data will be collected via established diagnosis tools and patient questionnaires (BSI, DC/TMD symptom questionnaire, DC/TMD examination form, GCPS, OHIP-G14). These forms can be found on the following webpages:BSI can be downloaded from the webpage of the DGFDT (https://www.dgfdt.de/richtlinien_formulare)DC/TMD symptom questionnaire, DC/TMD examination form and GCPS (version 2.0) can be found in different languages on the webpage of the International Network for Orofacial Pain and Related Disorder Methodology (INfORM—https://ubwp.buffalo.edu/rdc-tmdinternational/tmd-assessmentdiagnosis/dc-tmd-translations/). Specifications on how to assess and diagnose a patient in a standardized way can also be found on this webpage. This trial applied the German forms.OHIP-G14 can be accessed in German via the Institute of German Dentists (IDZ- https://www.idz.institute/fileadmin/Content/Publikationen-PDF/IDZ-2005-Fragebogen_OHIP-G-14.pdf).

The completed questionnaires are then assessed as specified by the DGFDT and INfORM. All forms are standard forms and are commonly applied in the context of bruxism and TMD. Validity and reliability of the DC/TMD are well characterized. A myalgia, myofascial pain, and arthralgia can be diagnosed with a sensitivity of ≥ 0.86 and a specificity of ≥ 0.98 and with an inter-examiner reliability for the clinical assessment of kappa ≥ 0.85 [30]. The GCPS is recognized as a sensitive tool to detect minor changes in TMD symptoms [20] and OHIP-G14 shows a correlation with self-perception of oral health and physical and mental dimensions and shows satisfactory validity and reliability [31, 32].

Furthermore, the volume change of splints and opposing dentition is calculated by overlaying optical scans with the software Geomagic Control X (3D Systems, Moerfelden-Walldorf, Germany) by trained users of the software.

### Plans to promote participant retention and complete follow-up {18b}

Participants are informed about the importance of their adherence and are motivated to follow trial guidelines. Further, participants receive the two splints for free to promote participant retention and complete follow-up. If a participant drops out of the trial or deviates from intervention protocols, the reason for discontinuation and deviation from the protocol will be recorded and it will be assessed on an individual basis if and how data generated during the trial can be implemented in statistical analysis.

### Data management {19}

Data is managed according to established protocols at the Medical Center, University of Freiburg meaning that treatment-relevant data is entered and stored electronically and revision safe in software that can only be accessed by personnel of the clinic via password from inside clinic buildings and via two-factor authentication from remote workstations. Data collected only for trial purposes is stored separately and can only be accessed by study personnel. This trial data is stored pseudonymized, meaning that the participant identifiers are replaced by a number, at the server of the aforementioned clinic. The list providing information on the allocation of numbers and participant identifiers is stored separately. If data needs to be transferred from one computer to another or from the intraoral scanner to a computer, the cloud provided by above-mentioned clinic is used for data transfer. Alternatively, if data transfer via cloud is not possible, encrypted mobile data storage media are used.

### Confidentiality {27}

All data of the participants is treated confidentially by the trial’s personnel. Data is collected via digital questionnaires and established assessment forms or is digitized after filling in paper documents. Then, data is stored as described above.

### Plans for collection, laboratory evaluation, and storage of biological specimens for genetic or molecular analysis in this trial/future use {33}

N/a because no biological specimens are collected.

## Statistical methods

### Statistical methods for primary and secondary outcomes {20a}

Absolute and relative frequencies are calculated for binary or categorical variables. For continuous data, the median, mean and standard deviation are specified. In addition, 95% confidence intervals are calculated. The calculations are performed per group (milled and 3D printed) and per cohort (bruxism and TMD). Cross-over effects are examined in all analyses. For the primary outcome parameter OHIP-G14, the group differences are estimated and tested using a linear regression model with corresponding two-sided 95% confidence intervals. The model will include the difference in OHIP-G14 values (milled vs. 3D printed) as a dependent variable and the sequence of the splints and the cohort (bruxism and TMD) as independent variables.

The one-sided test for non-inferiority of 3D printed versus milled splints at the 2.5% significance level is based on the two-sided 95% confidence interval of the linear regression model. The null hypothesis is rejected if the lower limit of the confidence interval for the difference (conventionally milled vs. 3D printed) is above − 5. The same applies to secondary outcomes, namely volume loss of the splint/opposing dentition, pain reduction, jaw mobility, and splint fracture rates.

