#### Secondary outcomes

Secondary outcomes are treatment efficacy and technical results of the stabilization splints. In the present trial, treatment efficacy is defined as the extent of abrasion of the opposing dentition in the bruxism cohort since the reduction of teeth abrasion is the therapeutic rationale for splint incorporation in bruxers. Teeth abrasion is measured as volume loss of the opposing dentition by superimposing intraoral scans obtained at digital impression taking and 3 months control appointments. Treatment efficacy in the TMD cohort is additionally investigated by quantification of pain reduction as the lead symptom of pain-related TMD. For this, the GCPS is evaluated on the day of incorporation and control appointments. The differences in the values obtained for chronic pain intensity (point score between 0 and 100), disability days (between 0 and 30), and interference score (point score 0–100) at control appointments and incorporation days are then calculated for every participant and splint type. Further, the number of painful points on examination according to the DC/TMD is compared at control appointments versus the incorporation date (range 0 to 48). Jaw mobility is investigated by measuring maximum jaw opening, laterotrusion, and protrusion in millimeters at incorporation and control appointments.

In addition, the technical results of 3D printed and milled stabilization splints are compared. Fit at incorporation is evaluated by calculating the amount of adjustment necessary in µm^3^ by overlaying scans before and after adjustment of the splint. Wear of the occlusal splints is assessed by calculating volume loss in µm^3^ by overlaying scans of the splints obtained at incorporation and the 3 months control. The integrity of the occlusal splints (no fracture of the occlusal splint) is assessed at control appointments, and the rate of fractures occurring is calculated in percent for each type of splint.

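### The OHIP-G14 rule (lower limit of milled minus printed above −5) is extended unchanged to the secondary outcomes: wrong side for jaw mobility, undefined sign for pain, effectively zero margin for splint wear

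*Protocol article*

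**What the plan says.** Section {20a} of the protocol article fixes one decision rule for the primary outcome: "The null hypothesis is rejected if the lower limit of the confidence interval for the difference (conventionally milled vs. 3D printed) is above − 5". It describes this as "The one-sided test for non-inferiority of 3D printed versus milled splints at the 2.5% significance level", read off the two-sided 95% interval of the regression model. The next sentence is: "The same applies to secondary outcomes, namely volume loss of the splint/opposing dentition, pain reduction, jaw mobility, and splint fracture rates".

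The figure 5 is introduced only in the sample size section {14}, which is based on OHIP-G14: "If the non-inferiority margin is set at 5 and a standard deviation of the differences of 10 is assumed". The article gives no other margin and no direction of benefit for any secondary outcome.

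The Secondary outcomes section lists quantities on quite different scales:

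- GCPS pain intensity and interference (each 0 to 100), disability days (0 to 30) and painful points (0 to 48), compared between control and incorporation visits.
- Mobility: "Jaw mobility is investigated by measuring maximum jaw opening, laterotrusion, and protrusion in millimeters".
- Splint adjustment and splint wear as volumes in µm³. Volume loss of the opposing dentition has no stated unit.
- Fractures: "the rate of fractures occurring is calculated in percent for each type of splint".

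**The concern.** A non-inferiority rule has two parts that belong to the outcome: which side of the interval is checked, and how far from zero the limit may lie. Both were chosen here for a 0 to 56 questionnaire score on which higher is worse. There, a worse printed splint makes milled minus printed negative, so checking the lower limit is correct. Where higher is better, a worse printed splint makes the difference positive and the lower limit moves further above −5. The rule then becomes easier to pass the worse the printed splint performs. Separately, 5 has no common meaning across points, millimetres, cubic micrometres and percent.

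This matters because the objectives section {7} makes therapeutic efficacy and technical outcome part of the non-inferiority question, and the background presents clinical non-inferiority as the precondition for the advantages of printing.

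**Working it through.** **The plan's own figure.** The only figure tied to the margin of 5 is the sample size: "38 participants are required for the trial with a two-sided paired t-test and a power of 90% on a 5% significance level". With SD 10, margin 5, one-sided 2.5% (two-sided 5%) and 90% power, the normal formula gives n = ((1.960 + 1.282) × 10/5)² = 42.03, so 43; the exact t version gives 44. Power at 38 is 85.1% and at 40 it is 86.9%. The 38 is therefore not reproduced. That is a separate matter and nothing below rests on it. What matters here is that 5 means OHIP-G14 points.

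**Side of the test, with difference = milled minus printed.**

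| Outcome | Better value | Sign if printed is worse | Does the lower limit guard against this? |
|---|---|---|---|
| OHIP-G14 | lower | negative | yes |
| Splint or antagonist volume loss | lower | negative | yes |
| Fracture rate | lower | negative | yes |
| Pain, control minus incorporation | lower | negative | yes |
| Pain, as a positive reduction | higher | positive | no |
| Jaw mobility (mm) | higher | positive | no |

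**Jaw mobility.** Inputs: n = 20 (the visit schedule examines the TMD patients), and a model with intercept and sequence, so 18 degrees of freedom and t = 2.101. The article gives no SD of differences, so 4 to 10 mm is assumed. The chance of passing is P(T > 2.101), where T is noncentral t with noncentrality (δ + 5)/(SD/√20) and δ is the true milled-minus-printed difference.

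- Printed 5 mm worse (δ = +5): at SD 10 the noncentrality is 10/(10/√20) = 4.47 and P = 0.988; at SD 8, P = 0.9995; at SD 4 or 6, P = 1.000.
- Mirrored rule (upper limit below +5), same truth: P = 0.025.
- Printed 5 mm better (δ = −5), rule as written: P = 0.025.

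**Pain intensity (0 to 100).** Printed 10 points worse, n = 20, assumed SD 15 to 25.

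| SD | Coded as positive reduction (δ = +10) | Coded control minus incorporation (δ = −10) |
|---|---|---|
| 15 | 0.988 | 0.0004 |
| 20 | 0.887 | 0.0013 |
| 25 | 0.718 | 0.0025 |

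**Splint wear.** 1 mm³ = 10⁹ µm³, so 5 µm³ = 5 × 10⁻⁹ mm³. With n = 40 and 37 degrees of freedom (intercept, sequence, cohort), t = 2.026. For an assumed SD of 0.001 mm³ (10⁶ µm³) the interval half-width is 2.026 × 10⁶/√40 ≈ 3.2 × 10⁵ µm³; for 10 mm³ it is 3.2 × 10⁹ µm³. Against either, 5 is nil, and the chance of passing when the splints are equal is 0.025.

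**Fractures in percent, 40 pairs.** One fracture is 100/40 = 2.5 points.

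- No fractures: the paired score (Tango) lower limit is −1.96²/(40 + 1.96²) = −8.8 points. The exact upper limit for 0 of 40 is 1 − 0.025^(1/40) = 8.8%. A t-type interval has zero width and passes. Clearing −5 with the score interval and no fractures needs 1.96² × 0.95/0.05 = 73 pairs.
- One printed-only fracture: the t-type lower limit is −2.5 − 2.026 × 2.5 = −7.6 and fails.
- Two milled-only fractures: the score lower limit is −4.2 and passes.

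**The case against.** The sentence may mean only that the method carries over, that is, a one-sided 2.5% test read from a two-sided 95% interval. The article condenses a full protocol that is not shown, and margins for individual outcomes could stand there. The primary comparison is unaffected. This lowers confidence that −5 will literally be applied to cubic micrometres, but it does not rescue the text: on that reading the listed tests have no margin and no direction in the article, and on the plain reading they have the wrong ones.

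Several stronger conclusions are tempting and are not supported:

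- *Pain is certainly tested on the wrong side.* The name pain reduction suggests so, but the Secondary outcomes section does not fix the order of subtraction, and OHIP-G14 is described as a difference from baseline. Coded that way, the rule is on the right side. What can be said is that the sign is undefined.
- *The fracture margin is impossible, or 5 points can never be shown with 40 pairs.* The rate is in percent, so −5 points is possible and on the right side. The rule would always pass only on a 0 to 1 scale, which is not the documented one. Two milled-only fractures would clear the limit.
- *The volume verdicts are meaningless or falsely favourable.* The side is right. The effect is a claim that is very hard to reach unless printed is truly better. The µm³ unit is stated only for the splint measures.
- *All secondary non-inferiority verdicts must go.* The objectives include these outcomes, so dropping the verdicts is one option, not a necessity.

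**Conclusion.** The concern holds: a rule specific to OHIP-G14 is stated as applying to outcomes with other units and, in part, the opposite direction.

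- **Jaw mobility:** wrong side without qualification. A printed splint that is truly 5 mm worse would be called non-inferior about 99% to 100% of the time, under assumed SDs of 4 to 10 mm and 20 participants.
- **Pain:** the verdict turns on an unstated coding. With printed 10 points worse, the pass probability is 0.72 to 0.99 under one coding and 0.0004 to 0.0025 under the other (assumed SDs 15 to 25).
- **Splint wear:** right side, effectively zero margin, so a superiority test in practice. This conclusion does not change over assumed SDs from 0.001 to 10 mm³. For the opposing dentition the margin cannot be interpreted, because no unit is given.
- **Fractures:** right side and a possible margin, but no justification. With no fractures at all, the verdict depends on the type of interval.

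The OHIP-G14 rule itself has the correct direction.

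**What to change.** Replace the carry-over sentence in {20a}. For each secondary outcome, state the order of subtraction, the unit and the direction of benefit. Then choose one of two routes, outcome by outcome:

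1. Report the milled-minus-printed estimate with its 95% interval and draw no non-inferiority verdict.
2. Give a justified margin in the outcome's own unit and test the harmful side. For jaw mobility that means the upper limit of milled minus printed lying below plus the margin. For pain, the side follows once the coding is fixed.

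State the unit for volume loss of the opposing dentition. For fractures, use a paired score or exact interval instead of a t-type interval.

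The cost is wording. No extra data or visits are needed. The trial may have to give up formal non-inferiority claims on outcomes for which no margin can be justified.
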